### Aims and hypotheses

The primary aim of this cRCT is to assess the effectiveness of SH+ on symptoms of psychosocial distress at 3 months. The secondary aim is to assess SH+ effectiveness using other measures of mental health and wellbeing from pre- to post-intervention, and at a 3-month follow-up. Additional aims are to assess: (1) whether psychological flexibility acts as a mediator of changes on other outcomes; (2) whether treatment effects are moderated by past experience of sexual and other forms of GBV, the number of different types of potentially traumatic events experienced and attendance at sessions. Health service use will be measured as an index of costs to enable preliminary cost-effectiveness analysis. We will assess fidelity to the intervention manual and contamination of the control group by exposure to SH+ materials or content.

We expect that women in the SH+ arm will show significantly greater improvements on all outcome measures both at immediate follow-up and 3-month follow-up compared with the EUC arm. In addition, we hypothesise that psychological flexibility will act as a mediator such that the intervention will lead to improvements in psychological flexibility, which in turn are associated with improvements on outcome measures.

Although the study is not powered to conclusively determine the moderation effects, we will conduct exploratory analyses of potential moderators. We expect smaller but still significant treatment effects for women exposed to GBV and higher levels of exposure to other potentially traumatic events. We also expect that treatment effects will be moderated by attendance such that greater attendance is related to larger effects.

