#### Moderators

To assess the level of exposure to different potentially traumatic events, we will administer an adapted 23-item version of the Harvard Trauma Questionnaire Part A (HTQ; Mollica *et al*. 1992) (*α* = 0.71). Respondents are asked whether they have experienced each of the events. For this study, several items were removed and others added based on contextual relevance in consultation with the local research and clinical team, and one item on torture was adapted from the original version of the HTQ. Two items on the HTQ Part A assessing domestic violence and sexual assault were replaced by three adapted items from the WHO Violence Against Women measure (World Health Organisation, 2005) that were perceived to enhance the ability of the scale to capture these experiences.

At T3, a single question will be asked about any potentially stressful or upsetting events participants have experienced during the trial period. Responses will be coded with general categories (e.g. violence, riots, hunger, destruction of home or property). PCAF reports will be used to identify additional community-level events that may affect particular villages.

A measure of attendance at sessions will be collected via session attendance sheets kept by intervention facilitators.

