### Enhanced usual care

EUC will be provided to participants in both SH+ villages as well as participants in control villages. We selected EUC as the comparator to avoid possible nocebo effects associated a waitlist condition (Furukawa *et al*. 2014), while providing more substantial support than usual care. It will consist of an individual visit from a Community Psychosocial Assistant (CPA; a trained Village Health Team member who is a South Sudanese refugee), employed on a small facilitation fee. The CPA will be aware of the allocation of the village and will provide information to all participants over one session of approximately 10–15 min held in the participant's home and covering: the effects of psychological distress; simple strategies to manage ‘overthinking’ (such as physical exercise, regular sleep and keeping a regular routine); services available via PCAF and how to access them. The CPAs will be of mixed sex. Other services will not be restricted in any way to participants in either condition, but will be monitored.

The standard PCAF services include assessments, and then based on need and preferences: psycho-education, group and individual psychological interventions, social work home visits, counselling, medication and group health talks. For SH+ participants, the CPA will also provide details of the SH+ programme and schedule of sessions.

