### SH+ implementation

The intervention will involve participants attending five weekly workshop sessions (20–25 people) lasting approximately 2 h each, during which pre-recorded audio materials adapted for the local context will be presented, with participants engaging in several experiential exercises and small group discussions. Participants will also be provided with a locally adapted illustrated self-help book to be used outside the sessions. Two facilitators will conduct the workshop, but their involvement will be minimal. Primarily, their role will be to coordinate the group process, for example, stopping and starting the audio, reading discussion exercises and answering basic questions from participants. The content of the intervention is delivered via the pre-recorded materials, with facilitators trained not to provide detailed explanations, in order to ensure fidelity and keep the need for their training and supervision minimal. A written facilitator guide helps facilitators to conduct the course.

SH+ involves teaching participants skills of: present moment awareness and grounding, defusion from and acceptance of difficult thoughts and feelings, identifying valued life directions and taking action in line with those, and compassion for self and others. A brief outline of the five sessions of SH+ is provided in Fig. 2. Skills learned in any session are reinforced in subsequent weeks.

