Second, we will add potential moderators and their interaction effects to explore variations in intervention effects. Trajectories of outcome measures will be compared between study conditions, while taking into account interaction effects with the following potential moderators of treatment effectiveness: exposure to GBV, trauma exposure to a large range of potentially traumatic events and attendance at sessions. As a secondary analysis, we will test whether baseline levels and types of distress act as moderators. This will be accomplished by creating interaction terms between study condition and moderators of interest. Significant interaction effects will be further probed utilizing model test statements.

Third, a mediation analysis will be conducted to determine whether increases in psychological flexibility with SH+, mediate improvements on: distress, functional impairment, hazardous alcohol use, feelings of anger, interethnic group relations, self-defined psychosocial goals, depression symptoms, PTSD symptoms and subjective wellbeing. In order to assess these mediation effects, we will conduct separate parallel process LGCM analyses (Cheong *et al*. 2003). A parallel process LGCM characterises participant-specific growth processes for a mediator and outcome variable simultaneously, and relates the growth processes with each other while also enabling an assessment of the influence of time-invariant and time-varying variables.

We will use full information maximum likelihood estimation (FIML) as implemented in Mplus 8.15 (Muthén & Muthén, 1998–2017) to adjust the estimates of the parameters to reflect missingness. FIML is considered the appropriate method for handing data missing at random (Schafer & Graham, 2002). Data will be checked prior to the implementation of FIML to address the assumption of missing at random. Results will be presented using point estimates, *p* values, odds ratios (when relevant) and 95% confidence intervals. Difference testing will be conducted to determine if the sample completing the intervention and follow-up assessments is significantly different from those who were lost to follow-up, in basic demographics as well as baseline variables.

Contamination within the EUC village participants (i.e. access to SH+ materials, or other content or messages) will be analysed descriptively. If substantial contamination is identified, contamination-adjusted analyses will be conducted.

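### Session attendance cannot be tested as a moderator by a condition-by-attendance interaction, because it varies only in the SH+ arm and arises after randomisation; what can be estimated is a within-SH+ association

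*Protocol article*

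**What the plan says.** The second modelling step in Statistics begins: "we will add potential moderators and their interaction effects to explore variations in intervention effects". Trajectories are to be compared between conditions, allowing for interactions with three named moderators: "exposure to GBV, trauma exposure to a large range of potentially traumatic events and attendance at sessions". Baseline distress is added as a further moderator in a secondary analysis. On method: "This will be accomplished by creating interaction terms between study condition and moderators of interest".

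Aims and hypotheses gives attendance a direction: "We also expect that treatment effects will be moderated by attendance such that greater attendance is related to larger effects". The same section says that the trial lacks the power to settle moderation and that these analyses are exploratory. The Abstract also names attendance as a potential moderator.

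The source of the variable is given under Moderators: "A measure of attendance at sessions will be collected via session attendance sheets kept by intervention facilitators". On the arms, SH+ implementation says: "The intervention will involve participants attending five weekly workshop sessions". Of EUC, which both arms receive, the article says: "It will consist of an individual visit from a Community Psychosocial Assistant". Villages are randomised after baseline and before the intervention starts (Participants, screening and randomisation).

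**The concern.** A moderator analysis asks whether the difference between arms changes with a characteristic that women in both arms have, and that allocation did not affect. Exposure to gender-based violence (GBV), trauma history and baseline distress fit that description. Attendance does not. EUC women have no workshops to attend, and SH+ women decide whether to attend after allocation, for reasons that may also bear on outcome. Statistics also plans a comparison of moderator scores between arms at baseline, and attendance has no baseline value.

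At stake is how one exploratory result is labelled. If the software drops the redundant column and reports the other, the output will look like the planned interaction. Because the article predicts its direction, a slope showing more improvement with more sessions could be reported as confirmed moderation when it may partly or wholly reflect who chose to attend.

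**Working it through.** **Inputs from the article.** Z = condition (1 = SH+, 0 = EUC). A = sessions attended, 0 to 5 in SH+ (SH+ implementation), with no workshops in EUC (Enhanced usual care). The planned total is 588 women, 294 per condition (Sample size). The article gives no figure for this point that could be reproduced.

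**Step 1: what the interaction means.** In a model with columns 1, Z, A and Z×A for the outcome's rate of change, the Z×A coefficient is the attendance slope in SH+ minus the attendance slope in EUC. With no variation in attendance in EUC, the second slope does not exist.

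**Step 2: coding EUC as 0.**
- EUC woman: Z = 0, A = 0, Z×A = 0.
- SH+ woman with no sessions: Z = 1, A = 0, Z×A = 0.
- SH+ woman with three sessions: Z = 1, A = 3, Z×A = 3.
- SH+ woman with five sessions: Z = 1, A = 5, Z×A = 5.

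Z×A = A in every row. A numerical check with 294 women per arm gave rank 3 for the four columns.

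**Step 3: any other constant.** If EUC women are coded c, then Z×A = A − c(1 − Z) in both arms, which is still an exact linear combination of the other columns.

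**Step 4: coding EUC as missing.** No EUC woman then supplies an attendance–outcome pair. Full information maximum likelihood has no EUC data from which to learn the second slope, and only SH+ women inform the term.

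**Step 5: what is left.** The columns 1, Z and A have full rank (3 of 3). The coefficient of A is the attendance–outcome slope within SH+. The coefficient of Z then compares SH+ women who attended nothing with all EUC women.

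**Step 6: can that slope arise without any effect?** Illustration with assumed values, none from the article: no treatment effect; an unmeasured standard normal factor U; probability of attending each session = logistic(0.85 + 0.8U); outcome = −0.5U + noise, total SD 1; one outcome, least squares, no village clustering. Over 2,000 simulated trials the attendance slope averaged −0.24 SD per session and was significant at the two-sided 5% level in all of them.

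Because the noise is independent of attendance, the expected slope is proportional to the loading on U, with factor 0.244/0.5 = 0.488:
- loading 0: slope 0
- loading −0.1: 0.488 × (−0.1) = −0.05 SD per session
- loading −0.25: 0.488 × (−0.25) = −0.12
- loading −0.5: −0.24

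The illustration shows the mechanism only. Its size is set by the assumed loading. Steps 1 to 5 need no such assumption.

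**The case against.** **The analysis is exploratory.** This is correct and limits the consequence: the primary outcome and the first modelling step are untouched. But the label covers imprecision. It does not create an attendance slope in EUC, and it sits beside a directional hypothesis.

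**The coding belongs in the analysis plan.** Statistics defers detail to an analysis plan signed before unmasking, which is not shown. However, the article itself fixes the variable, its role, the type of term and the expected result. No constant or missing coding of EUC attendance makes that combination estimable.

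**The interaction sentence might cover only baseline distress, which it follows.** The paragraph's opening and its second sentence already place attendance among the interactions.

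**A reader might infer that the model simply fails.** That goes too far. With one redundant column dropped it fits, and the attendance coefficient is interpretable as a within-SH+ association. The objection is to calling it moderation.

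**A reader might infer a known bias as large as the trial's detectable effect of 0.219.** The documents do not support this. A gap of 0.2 to 0.3 SD in prognosis between full attenders and non-attenders would be an assumption, and it is a different contrast from an intention-to-treat effect. The planned growth model also has participant-specific intercepts, which would absorb stable differences in level, so only confounding of change would remain. The simulation above has no such intercepts. On women's participation, the article reports only good adherence in the uncontrolled pilot.

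**A reader might infer that the result would steer scale-up.** The Discussion ties publication of the materials to sufficient evidence and leaves scalability to future work. Nothing links it to attendance.

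**Conclusion.** The point holds as a fault in what the article states. A condition-by-attendance interaction is planned for a variable that exists in one arm only, so it cannot be separated from the attendance main effect. The design is short by exactly one rank. The estimable remainder is a within-SH+ association of a post-randomisation variable with outcome, which self-selection can confound.

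This rests on attendance being constant or undefined in EUC, as the descriptions of the two arms imply. If a few EUC women did turn up at workshops, the columns would technically differ, but the EUC slope would rest on those contamination cases alone.

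The consequence is modest: one exploratory analysis could be misread as confirming a dose effect. The size of any confounding is unknown. Nor does a complier effect measure an error in the plan. Taking 0.219 at face value and assuming 90%, 80% or 60% attendance, it would be 0.219/0.9 = 0.24, 0.219/0.8 = 0.27 or 0.219/0.6 = 0.37, but that is a different estimand under assumed inputs.

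**What to change.** 1. Remove attendance from the moderator list (Abstract, Moderators, Statistics) and from the moderation hypothesis (Aims and hypotheses). With the article published, the place to do this is the analysis plan, before unmasking, with a note that it departs from the article.
2. Keep condition-by-moderator interactions for baseline variables: GBV exposure, trauma exposure and baseline distress.
3. Report attendance against outcome within SH+ descriptively, stating that it is non-causal.
4. Optionally, add a complier average causal effect with village allocation as the instrument, allowing for village clustering. Define compliance before unmasking. Any attendance is preferable to a higher threshold, because women below a threshold may still have been affected by the sessions they attended. State the exclusion restriction and its threats: the self-help book used outside sessions, partial attendance, and contamination in EUC. State also that precision will be limited with 14 villages. This answers a different question from the dose hypothesis, so it is not a required replacement.

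Items 1 to 3 cost only wording. Item 4 costs one secondary model on data already being collected.

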#### Use of services

To assess the use of EUC services by participants in both trial arms, an identifier will be added to the PCAF routine assessment to indicate whether the participant is in the SH+ trial. At the conclusion of the trial period, data will be gathered on access to any PCAF service (i.e. assessments, group support psychotherapy, medication, social work home-visits, counselling or group health talks).

To assess other health service usage, participants will be asked to list any health service they used for any health problem in the past month, including traditional healers. They will then be asked to identify expenditures in the past month on healthcare, through a series of nine questions.

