In terms of cost-effectiveness, we will apply a societal perspective on costs, including cost of services utilised by participants and losses in productivity. Primary analysis will be on total costs in previous 3 months at T1 and T3. Bootstrap sampling will be repeated 1000 times on skewed cost data. Cost-effectiveness ratios will be calculated by combining total costs with the different effectiveness measures.

Data will be double-entered from paper copies, and data management and descriptive analyses will be conducted in STATA 14.1 (StataCorp, 2015). Analyses testing hypotheses will be conducted using MPlus 8.15 (Muthén & Muthén, 1998–2017) and will be reported according to the CONSORT guidelines for cRCTs.

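### The primary cost analysis is defined on three-month totals, but participants are asked about service use and health spending over one month only

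*Protocol article*

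**What the plan says.** In the protocol article, Statistics sets the cost window: "Primary analysis will be on total costs in previous 3 months at T1 and T3". The same paragraph sets the perspective and two of its components: "we will apply a societal perspective on costs, including cost of services utilised by participants and losses in productivity".

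Use of services describes two data sources.

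- **Interview.** On services: "participants will be asked to list any health service they used for any health problem in the past month, including traditional healers". On spending: "They will then be asked to identify expenditures in the past month on healthcare, through a series of nine questions".
- **Records of PCAF, the implementing partner.** "At the conclusion of the trial period, data will be gathered on access to any PCAF service". An identifier added to PCAF's routine assessment marks the women who are in the trial.

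Aims and hypotheses gives a narrower basis for costs: "Health service use will be measured as an index of costs to enable preliminary cost-effectiveness analysis".

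On timing, Design places T2 at 6 weeks and T3 at 19 weeks; Statistics places T2 at 7 weeks.

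**The concern.** The window to be analysed is three times as long as the window asked about. This is a conflict between two statements in the same article. It is not a detail that can wait for the SAP, because an SAP can choose how to analyse data but cannot supply two months that the interview did not cover.

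Three things could happen in the analysis, and the article does not say which:

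- The recalled month is entered unscaled as a three-month figure. If use is steady, that part of the cost is understated threefold.
- The recalled month is multiplied by 3. This assumes steady use, and a one-off expense in the recalled month is tripled along with everything else.
- One month of recalled costs is added to PCAF records for a longer period. The total then mixes windows and gives the recalled part too little weight.

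These give different incremental costs, and so different cost-effectiveness ratios, from the same data.

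A second, weaker point is that productivity losses are promised as a cost component, but no measure in the article is presented as their source.

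**Working it through.** The plan gives no figure to reproduce here. The check compares the two windows.

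**Inputs**

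- Cost window: 3 months, at T1 and at T3 (Statistics).
- Recall window: 1 month, for services and for spending (Use of services).
- T3 at week 19 (Design and Statistics); T2 at week 6 (Design) or week 7 (Statistics).
- Conversion: 1 month = 365.25 / 12 / 7 = 4.35 weeks; 3 months = 13.04 weeks.

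**Step 1: coverage at T1.** 4.35 / 13.04 = 33%. About 67% of the window is not asked about.

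**Step 2: coverage at T3 from the T3 interview alone.** The window runs from week 19 − 13.04 = 5.96 to week 19. The recall runs from week 19 − 4.35 = 14.65 to week 19. Coverage is again 4.35 / 13.04 = 33%.

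**Step 3: coverage before T3 if the questions are also asked at T2.** This is an assumption.

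| T2 | T2 recall (weeks) | Overlap with the window | Added share | Total |
|---|---|---|---|---|
| Week 6 | 1.65 to 6 | 6 − 5.96 = 0.04 weeks | 0.3% | about 34% |
| Week 7 | 2.65 to 7 | 7 − 5.96 = 1.04 weeks | 8.0% | about 41% |

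An extra interview at T2 hardly helps, because its recalled month lies almost wholly before the three-month window opens.

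**Step 4: what PCAF records add.** They are collected at the end of the trial and could cover the 3 months before T3. They hold PCAF services only, so other providers, traditional healers and out-of-pocket spending remain on one-month recall. For the 3 months before T1, the article states no coverage by these records; the identifier that flags trial participants is introduced for the trial.

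**Step 5: productivity.** The outcome and service-use sections describe the measures one by one, often with item counts. None is presented as measuring lost work, income or time. The nearest is the 12-item WHODAS 2.0, which covers 30 days and is introduced as a measure of functional impairment. The aims name only health service use as the basis for costs.

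**The case against.** The strongest reply is that this is a condensed article with a full protocol and an SAP behind it, and that the analysis is preliminary and has no stated hypothesis. Setting also reports that PCAF provides all mental health services in the settlement, so the records may capture the services closest to the intervention. A threefold error would arise only if someone treated one month as three, which nothing in the article says will happen; applied to both arms, it would rescale the difference in recalled costs without reversing its sign.

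Much of this stands. It limits the consequence, and it means that the missing productivity measure may simply be described elsewhere. It does not remove the conflict between one month and three, because the interview also covers non-PCAF services and household spending on health, which the records do not.

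A reader might infer more than the article supports:

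- **That the cost of delivering SH+ is left out, so the ratio will favour SH+.** The list of components is introduced by a word that does not make it exhaustive, and unit costing is commonly left to the full documents. A three-month window before T3 opens at about week 6 and so misses most or all of the sessions. But delivery costs would normally come from programme accounts, and a participant recall window does not exclude them.
- **That the bootstrap ignores villages.** The resampling unit is not stated. The intracluster correlation of 0.012 in Sample size is a planning value for the trial's outcome and is not given for costs, so no size can be put on this.
- **That only about a quarter of the relevant period is observed.** This comes from dividing one month by the 19 trial weeks (4.35 / 19 = 23%), but the plan's own cost window is 3 months.

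**Conclusion.** The point holds for the windows. As written, the primary cost analysis cannot be computed from the data described without extrapolating non-PCAF service use and out-of-pocket spending. The interview covers about 33% of the window at T1. Before T3 it covers 33%, or between about 34% and 41% if T2 also carries the questions. These figures rest on calendar-month conversion, on the assessment weeks given in the article and, for the upper value, on T2 at week 7.

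On productivity the conclusion is limited to this: the article commits to the component and does not identify its source, and the aims describe a narrower cost basis. That calls for the source to be named or the perspective narrowed. It does not show that the data were not collected.

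The effect is confined to the cost-effectiveness analysis. The primary outcome and its analysis are not affected. The change is still worth making, because the Discussion presents SH+ as scalable with modest investment, and the cost results bear directly on that.

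**What to change.** Make the change before unmasking, while the SAP can still be settled. Trial status says that T3 data collection is in progress, so the recall period is largely fixed and the analysis should follow the data.

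1. Define the primary cost analysis on the window collected: past-month non-PCAF service use and healthcare spending at T1 and at T3.
2. If a three-month figure is wanted, state the scaling from one month as an assumption of constant use and test it in a sensitivity analysis.
3. Use PCAF records for PCAF services over the trial period. Report them for their own window, so that they are not added to one-month figures without adjustment.
4. Name the collected item that gives productivity losses. If there is none, drop the component and describe the perspective as health-service and out-of-pocket instead of societal.

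No new fieldwork is needed. The cost is a change of wording in the protocol and SAP, and possibly a narrower cost perspective than the one announced.

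### The primary cost variable covers the previous 3 months, but service use and health spending outside PCAF are asked about for the past month only

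*Protocol article*

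**What the plan says.** The cost-effectiveness paragraph of the Statistics section sets the perspective, "we will apply a societal perspective on costs, including cost of services utilised by participants and losses in productivity", and then the window: "Primary analysis will be on total costs in previous 3 months at T1 and T3". Cost-effectiveness ratios are to be formed from total costs and the various effectiveness measures.

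The data come from the Use of services section. For services outside the trial's own provision, "participants will be asked to list any health service they used for any health problem in the past month, including traditional healers". For spending, "They will then be asked to identify expenditures in the past month on healthcare, through a series of nine questions". Separately, PCAF's routine assessment carries an identifier for trial participants, and use of PCAF services is extracted once the trial period is over. That source does not depend on recall.

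The Aims and hypotheses section describes the cost measurement more narrowly: "Health service use will be measured as an index of costs". It calls the resulting analysis preliminary.

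**The concern.** The article states both the costing window and the recall period, and they differ by a factor of three. An analysis plan can settle many details later, but it cannot recover months that nobody was asked about. It can only extrapolate or redefine the variable, and the article announces neither.

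An analyst following the text would have two choices. One is to use one-month self-reported costs under a 3-month label. PCAF costs could span the full window before T3, so the total would then add components measured over different periods, and non-PCAF costs would be under-weighted. The other is to multiply the self-reported month by three. That assumes stable monthly costs and makes the cost difference less precise. Either way the numerator of every cost-effectiveness ratio would differ from the stated one, and a reader could not tell.

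**Working it through.** The article gives no cost figure to reproduce, so the check compares the windows and then sizes the two ways of bridging them.

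**Inputs**
- Costing window: 3 months before T1 and before T3 (Statistics).
- Recall: past month, for services and for spending (Use of services).
- T3 at week 19; T2 at week 6 (Design) or week 7 (Statistics). Both are used.
- One month = 365.25 / 12 / 7 = 4.35 weeks; three months = 13.04 weeks.
- Correlation r between a woman's monthly costs: not in the article, so assumed and varied.

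**Coverage at T1 and T3**
- 4.35 / 13.04 = 33%. The part never asked about is 13.04 − 4.35 = 8.70 weeks (from unrounded values), or two thirds.
- The window before T3 opens at week 19 − 13.04 = 5.96. Recall at T3 reaches back to week 19 − 4.35 = 14.65. Weeks 5.96 to 14.65 are therefore missing.

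**If the questions are also asked at T2 (assumption)**
- T2 at week 6: overlap with the window is 6 − 5.96 = 0.04 weeks, so coverage is (4.35 + 0.04) / 13.04 = 34%.
- T2 at week 7: overlap is 7 − 5.96 = 1.04 weeks, so coverage is (4.35 + 1.04) / 13.04 = 41%.
- For T1 there is no earlier assessment to add.

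**Used unscaled.** With a stable monthly mean, one month is 1/3 of the stated 3-month quantity.

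**Multiplied by three.** Let each month's cost have variance s², with correlation r between months.
- Var(3 × one month) = 9s².
- Var(sum of three months) = 3s²(1 + 2r).
- Ratio of standard errors = √[9 / (3(1 + 2r))] = √[3 / (1 + 2r)].

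| r (assumed) | Ratio |
|---|---|
| 0 | √3.00 = 1.73 |
| 0.2 | √(3/1.4) = 1.46 |
| 0.5 | √1.50 = 1.22 |
| 0.8 | √(3/2.6) = 1.07 |

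The ratio takes an error-free 3-month measure as comparator and leaves village clustering aside. It carries over to the clustered comparison if r is the same for village means as for women within villages.

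**The case against.** The strongest reply is that a 3-month figure can be produced. Multiplying a month by three is arithmetically simple, and a shorter recall may have been chosen on purpose. A reader might infer that the cost outcome cannot be computed at all, but the documents do not support that. What stands is that the article does not state the extrapolation that the two sections together require.

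Second, PCAF records soften the gap. The Setting section says PCAF provides all mental health services in the settlement, so that component could be complete for the window before T3. This is right, and it confines the gap to other health services and out-of-pocket spending. It also creates the mixed time base. A reader might go further and infer that PCAF use before T1 cannot be linked to trial participants. The article does not say whether earlier records of these women can be retrieved, so that remains open.

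Third, on productivity, a reader might infer that lost productivity was never measured. The article promises costs "including cost of services utilised by participants and losses in productivity", and none of the measures it describes records lost work, time or income. WHODAS 2.0 is described as rating difficulty over 30 days. But the article is condensed, the assessment schedule is a figure that is not shown, and the nine spending questions are not reproduced. Absence here is not proof, so this is only a secondary point to clarify.

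Finally, the analysis is preliminary and bears on no hypothesis about distress. That limits the consequence but does not remove the contradiction.

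**Conclusion.** The point holds as a contradiction between two explicit statements. The stated cost variable spans 3 months, while the self-reported data behind its non-PCAF part span one. About 33% of each window is observed (34% to 41% before T3 if T2 also carries the questions), and nothing else described in the article supplies the rest.

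The one-third understatement rests on stable monthly costs. The standard-error ratio of 1.73 to 1.07 rests on equal monthly variances and an assumed r of 0 to 0.8. The coverage figures need neither assumption. Coverage should be judged against the 3-month window and not against the 19 weeks of the trial, because the window is what the plan defines.

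The point should be corrected before the cost analysis is run. It does not touch the K6 comparison, the sample size or the randomisation.

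**What to change.** In the Statistics section, restate the primary cost variable as past-month total cost at T3, with past-month total cost at T1 as baseline. Restrict the PCAF records to the same month, so that all components share one time base and the ratios keep a defined numerator. State the source of the PCAF component at T1, and count each PCAF contact once if it is also self-reported.

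Report any 3-month total only as a sensitivity analysis, labelled as extrapolated from one month with the stable-cost assumption stated. Describe PCAF use over the whole follow-up separately.

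Keep the societal label only if a productivity item was collected, and then name it and its recall period. Otherwise describe the perspective by the components actually measured, and bring the Aims and hypotheses section into line.

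The change is to wording only and needs no new data. The article reports that T3 collection is under way, so the recall period is in practice fixed. The analysis plan is to be signed before unmasking and is the natural place for the correction. The price is a shorter cost window than the article promises.
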